### Statistical Analyses

Descriptive statistics will be used to characterize the sample. For the analysis of the primary outcome, the social integration, and support subscale of the HeiQ, we will evaluate the difference in change scores between groups using a mixed-effects model that takes into account the repeated measures of the outcome. The model will incorporate the strata of sex and method of recruitment, as well as control for sociodemographic covariates such as age and sex.

With the exception of the data collected for the economic analysis, all other continuous outcomes (our secondary outcomes), including the other 7 subscales of the HeiQ, will also be assessed using a mixed-effects model. In addition, we will investigate whether there are associations of the primary and secondary outcomes with sex, urban or rural residence, disease status, and eHealth literacy. Nonnormally distributed continuous variables will be transformed prior to analyses. All analyses will be tested using an alpha of.05.

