### Sample Size Estimate

Data from our single-group, pre-post pilot study that examined the proof-of-concept of the Healing Circles program [25] indicated an expected effect size of 0.58 in our primary outcome, the difference in the change in the social integration and support subscale of the Health Education Impact Questionnaire (HeiQ) Version 3 [26]. For this study, we selected a more conservative effect size of 0.33 that is, a mid-to-large effect based on Cohen *f* mid effect (0.25) plus large effect (0.40) divided by 2 [27] to account for comparison between the 2 groups (of note, this estimate may increase slightly in the Usual Care group) and the fact that the parameter estimates from our small pilot study may be highly variable. With an alpha of.05, we calculated a sample size of 198 to have 90% power. To adjust for an expected loss to follow-up rate of ~20%, over the duration of the study, we will recruit a sample size of 250 (125 per group) to retain 198 participants at the study end.

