### Randomization and Interventions

After the baseline assessment, participants will be stratified by sex and recruitment site, and randomized using Web-based, computer-generated, random block sizes of 4 and 6 in a 1:1 manner to either the Usual Care or the Healing Circles group. A member of the research team who is not involved with recruitment, assessments, or study intervention will perform the randomization procedures.

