### Study Outcome Measures

The primary outcome is the difference in the change in the social integration and support subscale of the HeiQ Version 3 [26] between the Healing Circles and Usual Care groups. HeiQ is a self-management measure developed using Item Response Theory, comprising 8 self-management subscales as follows: health directed activity (4 items); positive and active engagement in life (5 items); emotional distress (6 items); self-monitoring and insight (6 items); constructive attitudes and approaches (5 items); skill and technique acquisition (4 items); social integration and support (5 items); and health service navigation (5 items). Each item is scored using a 4-point response scale (1=strongly disagree; 2=disagree; 3=agree; 4=strongly agree). A mean score is derived for each subscale with higher scores indicating better self-management ability, with the exception of the emotional well-being subscale where a higher mean score is indicative of lower self-management ability.

We selected the 5-item social integration and support subscale as our primary outcome because the items align closely with the Healing Circles intervention, and results from our pilot study suggested that this subscale is most responsive to changes as a result of the Healing Circles program [25]. Moreover, this subscale has been shown to have high internal consistency reliability (Cronbach alpha=.86) [26].

Secondary outcomes include the 7 other subscales within the HeiQ as well as several other variables as follows. *Self-efficacy* will be measured using the 6-item Self-efficacy for Managing Chronic Disease Scale [29]. This 6-item scale covers several domains that are common across many chronic diseases, including symptom control, role functioning, emotional functioning, and communicating with physicians and has high internal consistency reliability (Cronbach alpha=.91) [29]. Responses for each item range from 1 (not at all confident) to 10 (totally confident). Higher mean scores indicate higher self-efficacy.

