## Results

### Assessments

#### Baseline

Baseline will consist of the collection of our primary and secondary outcomes that require pre and post measurements, as well as social demographic data, medical history, and eHealth literacy using the eHealth Literacy Scale (eHEALS) [45], to assess the participants’ use of technology to access and evaluate health information. The eHEALS is used to assess the combined knowledge, comfort, and perceived skills at finding, evaluating, and applying electronic health information to health problems.

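### The primary analysis compares change scores without adjusting for baseline HeiQ, so a valid analysis gives up precision and stays exposed to chance baseline imbalance

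*Protocol article*

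**What the plan says.** Three places in the protocol article fix the primary comparison.

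- **Study Outcome Measures:** "The primary outcome is the difference in the change in the social integration and support subscale of the HeiQ Version 3", compared between the two groups. Sample Size Estimate describes the outcome in the same terms.
- **Statistical Analyses, method:** "we will evaluate the difference in change scores between groups using a mixed-effects model that takes into account the repeated measures of the outcome".
- **Statistical Analyses, covariates:** "The model will incorporate the strata of sex and method of recruitment, as well as control for sociodemographic covariates such as age and sex".

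Two further places show that the baseline score is available and is not controlled by design.

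- **Baseline:** "Baseline will consist of the collection of our primary and secondary outcomes that require pre and post measurements".
- **Randomization and Interventions:** "After the baseline assessment, participants will be stratified by sex and recruitment site". The baseline HeiQ score is therefore known before allocation and is not a stratification factor.

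No section names the baseline HeiQ score as a covariate or says that baseline means are constrained to be equal.

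**The concern.** A comparison of change scores subtracts the whole baseline value from each follow-up value, which fixes the coefficient on baseline at 1. With equal variances at the two times, the regression coefficient of follow-up on baseline equals rho, which is below 1 whenever the two measurements are not perfectly correlated. Subtracting too much baseline has two consequences:

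- baseline noise is carried into the estimate, so its variance is larger than it needs to be;
- if one arm happens to start higher, the estimated difference in change is pulled in the opposite direction.

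Both affect the primary endpoint. They can be avoided with a measurement that the trial already takes before randomization.

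**Working it through.** **Inputs**

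- Number analysed: 198, so 99 per arm at 1:1 (Sample Size Estimate).
- Effect size: "we selected a more conservative effect size of 0.33".
- Alpha: "All analyses will be tested using an alpha of.05". The article does not state sidedness; two-sided is assumed.
- rho, the correlation between baseline and follow-up score: not in the documents; assumed 0.3 to 0.8.
- Score SD (s): assumed equal at baseline and follow-up and in both arms.

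**The plan's own figure.** 198 at 90% power does not follow from these inputs. Read as a standardized difference, 0.33 needs 2 x (1.960 + 1.282)^2 / 0.33^2 = 193 per arm, 386 in total. Read as Cohen f for two groups, it needs about 99 in total. The dropout step does reproduce: 198/0.8 = 248, against 250 stated. The sample size is a separate matter. Here 198 serves only as the number analysed, and the variance ratio does not depend on it.

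**Precision at a single visit, n per arm**

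- Change score: Var = (2/n) x 2s^2(1 - rho)
- Baseline-adjusted: Var = (2/n) x s^2(1 - rho^2)
- Ratio, adjusted to change: (1 - rho^2) / [2(1 - rho)] = (1 + rho)/2

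At rho 0.5 and n = 99 the variances are 0.0202 s^2 and 0.01515 s^2, a ratio of 0.75.

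**Shift from imbalance.** Given an observed baseline difference D, the change-score estimate is displaced by -(1 - rho)D. A difference of one standard error is D = sqrt(2/99) = 0.142 SD.

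| rho | Variance ratio | Change-score N matching 198 adjusted (198/ratio) | Adjusted N matching 198 by change score (198 x ratio) | Shift for D = 0.142 SD | Shift as share of 0.33 SD |
|---|---|---|---|---|---|
| 0.3 | 0.65 | 305 | 129 | 0.099 SD | 30% |
| 0.5 | 0.75 | 264 | 149 | 0.071 SD | 22% |
| 0.7 | 0.85 | 233 | 169 | 0.043 SD | 13% |
| 0.8 | 0.90 | 220 | 179 | 0.028 SD | 9% |

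The last column reads 0.33 in SDs of the score itself.

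**Power.** If 0.33 is instead a standardized difference in SDs of the change, 99 per arm gives 0.64 by change score. Adjustment gives 0.82, 0.77, 0.71 and 0.69 at rho 0.3, 0.5, 0.7 and 0.8. If 0.33 is Cohen f (a standardized difference of 0.66), power exceeds 0.99 already, and what adjustment adds is narrower intervals and protection against imbalance.

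**Does the mixed model recover the loss by itself?** Take five visits, compound symmetry, complete data and 99 per arm.

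- Baseline as one of the repeated outcomes, with free means in each arm: the single-visit contrast at rho 0.5 has variance 0.0202 s^2, exactly that of the change score.
- Baseline means constrained equal: 0.01515 s^2, exactly that of baseline adjustment.
- For the average of four follow-up visits, the constrained-to-free ratio is 0.44, 0.60, 0.76 and 0.84 at rho 0.3, 0.5, 0.7 and 0.8. The article does not say that this average is the contrast, so the single-visit figures are the ones to rely on.

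**The case against.** The strongest reply is that the article states an estimand, the difference in change, and a model class, and leaves the rest open. A mixed-effects model of repeated measures can be a constrained longitudinal model, and an unseen analysis plan may specify one or add a baseline term. That is possible, but the article does more than stay silent: it names change scores as what is compared and names the covariates. The covariate list is open-ended only for sociodemographic variables, and a baseline HeiQ score is not one. The two natural readings of the text are change as the response, or a group-by-time contrast with baseline means left free. Both give change-score precision at a single visit.

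Several limits do stand, and a reader might infer more than the text allows.

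- **That the analysis is biased or invalid.** It is not. Under randomization the change-score estimate is unbiased on average. The shift is conditional on the imbalance that happens to occur.
- **That ceiling effects put the baseline coefficient far below 1.** The article gives no baseline distribution, SD or ceiling rate, and no rho. The size of the loss is a range, and at rho 0.8 it is modest.
- **That an unconstrained mixed model always equals a change-score analysis.** The equality shown is for complete data at a single visit. Follow-up here runs from 6 to 24 months with about 20% loss, so it will not hold exactly.
- **That the secondary outcomes are affected in the same way.** For them the article says only that a mixed-effects model will be used as well; change scores are not mentioned.
- **That power falls below what was planned.** The trial was sized on the difference in change, so analysing change matches the stated design. The loss is relative to a better analysis of the same data.

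**Conclusion.** The point holds as one of efficiency and of conditional imbalance on the primary endpoint. Followed as written, the article's analysis leaves out a prognostic baseline measurement that is already in hand.

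For a single visit with equal variances, adjustment removes 35%, 25%, 15% or 10% of the variance at rho 0.3, 0.5, 0.7 or 0.8. A one-standard-error baseline difference moves the change-score estimate by 0.099 to 0.028 SD over the same range. These figures rest on an assumed rho. The direction does not: under equal variances the ratio is below 1 for every rho below 1. The change is worth making but does not bear on the validity of the trial.

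**What to change.** Reword the primary model in Statistical Analyses in one of two ways:

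1. a repeated-measures mixed model of the follow-up scores, with group, visit, group-by-visit, the stratification factors, the baseline subscale score and its interaction with visit; or
2. a constrained longitudinal model, with baseline among the repeated outcomes and a common baseline mean across arms.

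Either keeps the between-group difference in change as the estimand. If the other 7 HeiQ subscales and self-efficacy are meant to follow the primary model, say so and use the same form. If an analysis plan already adjusts for baseline, bring the protocol wording into line with it.

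The cost is a sentence or two of analysis text. No new data, visits or participants are needed. Settle the wording before any comparison by group is run, so that the choice between change-score and adjusted results cannot be made after seeing them.

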### Economic Analyses

The primary framework for the economic analysis will be a cost-consequence analysis, where resource use, costs, and outcomes of the 2 treatment groups are listed separately in a disaggregated format (eg, hospital costs, out-of-pocket expenses, self-management outcomes, health-related quality of life, and capability well-being). The time horizon for the cost-consequence analysis will complement the study’s design for the follow-up to maximize the use of available data (ie, 0-6, 0-12, 0-18, and 0-24 months).

We will also perform a cost-utility analysis from the perspective of the publicly funded health care payer, in line with recommendations from the Canadian Agency for Drugs and Technologies in Health [43]. Health outcomes will be expressed as QALYs, with QALY estimates generated from EQ-5D-5L responses using a Canadian value set [44]. The time horizon for the cost-utility analysis will be dependent on the sample sizes observed at 12-, 18-, and 24-month follow-up. In addition, differences between groups in costs and QALYs will be expressed using the cost-per-QALY ratio, which provides an estimate of the additional cost required to gain each additional unit of outcome.

## Results

### Assessments

#### Baseline

Baseline will consist of the collection of our primary and secondary outcomes that require pre and post measurements, as well as social demographic data, medical history, and eHealth literacy using the eHealth Literacy Scale (eHEALS) [45], to assess the participants’ use of technology to access and evaluate health information. The eHEALS is used to assess the combined knowledge, comfort, and perceived skills at finding, evaluating, and applying electronic health information to health problems.

#### Follow-Up

Every 6 months between randomization and the study’s end (anticipated in December 2019), participants will undergo an assessment of outcomes only. Those recruited at the end and beginning of recruitment will experience follow-up periods ranging from 6 to 24 months (2 years), respectively. We expect an average of 18 months of follow-up. In addition, we anticipate that the main effects on self-management will occur early after randomization; however, extended follow-up will allow us to investigate the sustainability of any observed effect, Healing Circles’ use over time, and health care use for an extended period. Participants may complete data collection either in-person with a blinded assessor, self-report through mailed responses, or on the Web. The study started recruitment in September 2017. Individuals are still currently being recruited for participation, and existing participants are currently on follow-up.

## Discussion

Healing Circles is a novel program aimed at improving self-management through peer support, as well as recovery from and management of CVD. Given our real-world study design and the participatory aspects of engaging end users, our findings could be readily translated into practice. If the results support our hypotheses, it will indicate that Healing Circles is an effective intervention for improving self-management and reducing health care use. If so, this robust assessment of the implementation and use of Healing Circles could be used to inform future design of the program and inform plans for scale-up.

## Appendix

Multimedia Appendix 1 Peer-reviewer report from the Canadian Institutes of Health Research.

## Abbreviations

CVD: cardiovascular disease
eHealth: electronic health
EQ-5D-5L: EuroQoL-5 dimension 5-level version
HeiQ: Health Education Impact Questionnaire
ICECAP-A: ICEpop CAPability measure for Adults
mHealth: mobile health
QALY: quality-adjusted life year
